## Abstract

**Background:**

Cesarean delivery has already become a very common method of delivery around the world, especially in low-income countries. Hypertrophic scars and wound infections have affected younger mothers and frustrated obstetricians for a long time. Mesenchymal stem cells (MSCs) have strong potential for self-renewal and differentiation to multilineage cells. Previous studies have demonstrated that MSCs are involved in enhancing diabetic wound healing. Therefore, this study is designed to investigate the safety and efficacy of using MSCs in the treatment of Cesarean section skin scars.

**Methods:**

This trial is a prospective, randomized, double-blind, placebo-controlled, single-center trial with three parallel groups. Ninety eligible participants will be randomly allocated to placebo, low-dose (transdermal hydrogel MSCs; 3 × 10^6^ cells) or high-dose (transdermal hydrogel MSCs; 6 × 10^6^ cells) groups at a 1:1:1 allocation ratio according to a randomization list, once a day for six consecutive days. Study duration will last for 6 months, comprising a 1 week run-in period and 24 weeks of follow-up. The primary aim of this trial is to compare the difference in Vancouver Scar Scale rating among the three groups at the 6th month. Adverse events, including severe and slight signs or symptoms, will be documented in case report forms. The study will be conducted at the Department of Obstetric of Southern Medical University Affiliated Maternal & Child Health Hospital of Foshan.

**Discussion:**

This trial is the first investigation of the potential for therapeutic use of MSCs for the management of women’s skin scar after Cesarean delivery. The results will give us an effective therapeutic strategy to combat Cesarean section skin scars, even with uterine scarring.

**Trial registration:**

ClinicalTrials.gov, NCT02772289. Registered on 10 May 2016.

**Electronic supplementary material:**

The online version of this article (10.1186/s13063-018-2478-x) contains supplementary material, which is available to authorized users.

## Background

Over the past decades, Cesarean delivery has already become a very common method of delivery around the world, especially in low-income countries [1]. In China, although the Cesarean rate has decreased in individual megacities, the overall annual rate has still increased, reaching 34.9% in 2014, from 28.8% in 2008 [2]. Hypertrophic scars and wound infections have affected younger mothers and frustrated obstetricians for a long time. As one of the top three hospital-acquired infections, wound infections can prolong hospitalization and greatly increase the rates of hospital readmission, risk of death, and overall costs of healthcare [3]. It is reported that the incidence of wound infections ranges from 3% to 20% in women after Cesarean delivery [4]. In addition, hypertrophic scars and psychological stress are causes of dissatisfaction in women after Cesarean delivery.

The cutaneous wound healing process is very complex. It requires a variety of cells to collaborate, such as resident cells of the skin, hematopoietic cells, and immune cells [5]. Many complex factors, such as abnormal macrophage polarization, abnormal keratinocyte and fibroblast migration, proliferation, differentiation and apoptosis, impaired recruitment of mesenchymal stem cells (MSCs) and endothelial progenitor cells, and decreased vascularization may contribute to an abnormal wound healing process [6–8]. It is also reported that enhanced and prolonged expression of tumor necrosis factor-alpha contributes to abnormal wound healing processes [9, 10].

Hypertrophic scarring is a fibrotic disease, arising from fibroproliferation disorder, which occurs after the damage of the deep dermis by deep skin injury, surgical procedure, or burns [11]. Overproduction of extracellular matrix and collagens are considered to be the main pathological characteristics of hypertrophic scars [12, 13]. Key cell subpopulations, including deep dermal fibroblasts, myofibroblasts, fibrocytes, and T-helper cells, could both modify and interact with the extracellular matrix of the wound, ultimately forming a hypertrophic scar [14]. Abnormal wound healing processes can also cause bacterial proliferation. In some instances, the bacterial load increases sufficiently for infection to ensue [15]. Therefore, an abnormal wound healing process could increase the risk of hypertrophic scarring and wound infection. In turn, continuous inflammation and bacterial proliferation also increase the risk of abnormal wound healing processes.

Post-Cesarean wound infection has been ascribed to many factors, including obstetrician-related factors, such as skin incision type, time of operation, suture technique, or intraoperative blood loss, and maternal factors, such as intrauterine infection prior to delivery, presence of comorbidities, or body mass index [16, 17]. Antibiotics, wound exploration, and debridement are mainstays in the medical care of post-Cesarean wound infections at present [18]. Many therapeutic approaches, such as laser therapy, radiation, cryotherapy, cryosurgery, or intralesional injections of corticosteroids, have also been reported in the management of hypertrophic scars [19]. However, many of them are involved in high rates of recurrence, and many are also expensive and painful.

Mesenchymal stem cells are a population of pluripotent stem cells. They possess high potencies of self-renewal and differentiation into canonical cells of the mesenchyme [20]. They are initially discovered in bone marrow and are subsequently found in almost every type of tissue, including the endometrium, placenta, umbilical cord, adipose tissue, and gingiva [21]. They have been reported as an effective and successful treatment for many diseases, including rheumatoid arthritis [22], experimental autoimmune encephalomyelitis [23], bone regeneration [24], and ischemic cardiomyopathy [25]. As a treatment modality, MSCs have demonstrated great potential value.

Through their migratory, anti-inflammatory, and trophic properties, MSCs exert numerous functions that may be of relevance for restoring skin tissue function and enhancing healing [26]. Using a rabbit model, researchers found that human MSCs can regulate inflammation and prevent the formation of hypertrophic scars [27]. Previous results of clinical trials also demonstrated the benefits derived by the employment of MSCs in wound healing [28, 29]. Falanga *et al.* [30] indicated that MSCs can be safely and effectively delivered to wounds using a fibrin spray system. Another clinical trial showed that directly applied bone marrow-derived cells can lead to dermal rebuilding and closure of nonhealing chronic wounds [31]. Yoshikawa *et al.* [32] demonstrated that MSCs are therapeutically effective in patients with intractable dermatopathies. In addition, Dash *et al.* [33] showed that autologous implantation of bone marrow-derived MSCs in nonhealing ulcers accelerated the healing process and significantly improved clinical parameters.

In this trial, we hypothesize that MSCs can reduce hypertrophic scars and decrease wound infection after Cesarean delivery. Therefore, we undertake a Phase II clinical trial to evaluate the safety and efficacy of MSCs in the treatment of Cesarean section skin scars in a prospective, randomized, double-blind, placebo-controlled, single-center study.

## Methods

### Study design

This study protocol conforms to the Standard Protocol Items: Recommendations for Interventional Trials (SPIRIT) guidelines (see Fig. 1 and Additional file 1). The trial is intended to target primiparous women between the 37th and 42nd weeks of gestation. Trained out-patient doctors will introduce the details of the trial to each potential participant during a clinic visit. The trial coordinator will contact the interested participant by mobile phone and WeChat, a very popular social networking app in China [34]. Eligible participants will be introduced in the trial. The inclusion and exclusion criteria and trial flow are shown in Table 1 and Fig. 2, respectively. The selection, information process, and randomization will be implemented as soon as we know that the primiparous woman is going to have a programmed Cesarean delivery. There is about 1 day between selection and delivery. The Cesarean delivery will be programmed for a gestational age ≥ 37 weeks and < 42 weeks. This trial will be a prospective, randomized, double-blind, placebo-controlled with three parallel groups. The trial will be conducted at the Department of Obstetric of Southern Medical University Affiliated Maternal & Child Health Hospital of Foshan.

**Fig. 1 Fig1:**
[figure not shown]
SPIRIT figure

**Table 1 Tab1:** Eligibility criteria

Inclusion criteria	Exclusion criteria
Primiparous women receiving Cesarean delivery	Any systemic uncontrolled disease
Aged 21–35 years	Recent or current cancer
Gestation age ≥ 37 weeks and < 42 weeks	History of or presenting with a keloid formation
Willing to sign an informed consent form and a photographic release form	Wounds or local disease in treatment area
Willing to comply with study dosing and complete entire course of study	Planning any other cosmetic procedure to the study area during the study period
	Smoking

**Fig. 2 Fig2:**
[figure not shown]
Trial schema

### Interventions

Eligible participants, who have signed informed consent forms, will be randomized to placebo, low-dose (3 × 10^6^ cells) or high-dose (6 × 10^6^ cells) groups, receiving transdermal hydrogel MSCs or placebo once a day for six consecutive days. Each pump dispenses 1.0 ml gel (including 1 × 10^6^ cells or none). The justification of doses is based on previous studies for other indications [35, 36] and our preliminary experiment (unpublished). Each pump, either MSCs or placebo, has the same external characteristics except for a digital tag, to allow blinding of the intervention. After suturing the skin incision as usual, the first intervention will take place on the operating table and the remaining five interventions will take place in the postnatal ward. Participants in the placebo group will receive placebo hydrogel once a day for 6 days; those in the low-dose group will receive one dose of hydrogel with cells once a day for three consecutive days and then placebo hydrogel for the next three consecutive days; those in the high-dose group will receive cells for 6 days.

The government has been committed to promoting cooperation between governments, academia, pharmaceutical companies, biotechnology firms, and private investors to research and evaluate MSC therapies, since they are advanced therapies [37, 38]. The Health-Biotech Pharmaceutical Company (Beijing, China) manufactures both MSCs and the placebo hydrogel. The products will be provided without charge. The MSCs are extracted from the umbilical cord, which is donated by a healthy donor who has provided informed consent. Detailed descriptions of the method have been given in a previous article [39].

The study duration will last for 6 months, including a 1 week run-in period and 6 months of follow-up. All participants will be assessed at 0.5, 1, 3, and 6 months during the follow-up period. Table 2 provides the time points and specific measurements of data. Cosmetic use may affect wound function. If participants use cosmetics in the follow-up period, they will be withdrawn from the study.

**Table 2 Tab2:** Schedule of visits and assessments

Time point (weeks)	2	4	12	24
Vancouver Scar Scale		√	√	√
REEDA scale	√			
Erythema		√	√	√
Pigmentation		√	√	√
Scar thickness		√	√	√
Scar area		√	√	√
Immunoglobulin		√	√	√
Satisfaction		√	√	√
Adverse events	√	√	√	√

REEDA, Redness, Edema, Ecchymosis, Discharge, Approximation

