### Sample size

Our sample size calculation is based on previous results from [name] preliminary trial in Taipei Medical University WanFang Hospital [42]. These results found that the mean VSS was 4.50 ± 1.68 in healthy pregnant women. The ratio of the MSC and control group sample size sets was 2:1. We will use the conventional values *α* = 0.05 and *β* = 0.1 for two-sided tests of probability. Meanwhile, we hypothesize that the difference in mean VSS at 6 months after treatment between the MSCs and placebo group will be *δ* = 1.5. The total sample size is estimated to be 74. Considering a dropout and other potential influencing factors, the final participant is estimated to be about 90 (*n* = 30 in each group).

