### Randomization, concealment, and blinding

A computerized random number generator will be used to produce a randomization schedule employing simple randomization by an independent clinical researcher, who is not involved in the recruitment, intervention, assessment, or statistical analysis. During the study period, the independent clinical researcher will retain the randomization list. The randomization sequences will be concealed in lightproof, sealed envelopes. After signing informed consent forms, eligible participants will be randomly allocated to the three parallel groups at a 1:1:1 allocation ratio, according to the randomization list.

Each participant will receive a unique randomized number. Meanwhile, each participant’s pump will be labeled with a unique randomization number, which will become the participant’s number. Direct participants and investigators, including the outcome assessors and statisticians, will be blinded to the allocation status throughout the study. Once participants have been allotted randomized numbers, a reasonable effort will be made by investigators to avoid missing data.

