### Statistical analysis

All analyses will be conducted on the intention-to-treat and per-protocol principles. Regardless of whether participants received the randomized treatment, the intention-to-treat principle considers all of them as randomized. A complete case analysis will be performed if missing data for the randomized participants accounts for less than 5% of total data. Multiple imputations will be used if missing data is more than 5%. Dropouts will be included in the analysis by multiple imputations for missing data. The effect that the per-protocol participants and missing data might have on results will be assessed via sensitivity analysis. Subgroup analysis will be performed based on age and gestational age.

The primary comparison, both doses vs. placebo, will be analyzed using a superiority analysis. We will use the *t* test for the continuous outcome. Meanwhile, high dose vs. placebo and low dose vs. placebo will also be analyzed using the *t* test. Other outcomes will be analyzed using noninferiority analysis. The mean (and standard deviation) will be expressed for continuous variables, and numbers (percentages) will be expressed for categorical variables. Group variances will be compared using Leven’s test at the 0.05 significance level. Analysis of variance (ANOVA) will be used to analyze continuous data, and the *chi*-square test or Fisher’s exact test will be used for categorical data. To investigate the effects of treatment and time course, repeated measures ANOVA will be applied to determine changes in the continuous outcome data at each visit. R 3.1 software will be used for analysis.

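### The VSS comparisons are fixed as unadjusted t tests after simple randomization; a short pre-treatment covariate list would cheaply add precision and protect against chance imbalance, mainly for the single-dose comparisons

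*Protocol article*

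**What the plan says.** All references are to the Protocol article.

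- **Interventions:** the gel is first applied after closure: "After suturing the skin incision as usual, the first intervention will take place on the operating table". The article gives no closure method and no number of operators.
- **Background:** wound infection after Cesarean delivery is attributed to "obstetrician-related factors, such as skin incision type, time of operation, suture technique, or intraoperative blood loss, and maternal factors", and BMI is among the maternal factors. The same section says that abnormal healing can raise the risk of both hypertrophic scarring and wound infection.
- **Randomization, concealment, and blinding:** the schedule is produced "employing simple randomization by an independent clinical researcher". No stratification factor is named.
- **Statistical analysis:** the primary comparison is both doses against placebo, tested for superiority: "We will use the *t* test for the continuous outcome". Each dose against placebo is also a t test. The only patient characteristics named for the analysis are age and gestational age, as subgroup factors.
- **Table 1:** age is limited to 21–35 years and gestation to 37 to under 42 weeks. BMI is not limited.

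**The concern.** The article names characteristics that bear on wound healing, yet neither the allocation nor the stated tests use any of them. The two characteristics that do enter the analysis, age and gestational age, are already narrowed by eligibility and are not in the Background's list of examples.

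If BMI, incision type or closure type explains some of the variation in 6-month VSS, an unadjusted comparison leaves that part in the error term. With about 30 women per arm and simple randomization, one arm may also by chance hold more women with a less favourable characteristic, and the t test makes no correction for it. This matters most for the two single-dose comparisons. They have the fewest women, and the Discussion relies on the trial to identify an effective dose.

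**Working it through.** **Inputs (Sample size section).** Error rates: "We will use the conventional values *α* = 0.05 and *β* = 0.1 for two-sided tests of probability". Standard deviation (SD) 1.68: "These results found that the mean VSS was 4.50 ± 1.68 in healthy pregnant women". Effect 1.5: "the difference in mean VSS at 6 months after treatment between the MSCs and placebo group will be *δ* = 1.5". Ratio: "The ratio of the MSC and control group sample size sets was 2:1". The stated total is 74 before dropout and 90 after, or 30 per arm. The share of VSS variance explained by the covariates (R²) is not in the documents. It is **assumed** at 0, 0.05, 0.10 and 0.20.

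**Step 1: the plan's own figure.** For two means at 2:1, with the normal approximation:

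n(control) = (1 + 1/2) × [(1.960 + 1.282) × 1.68 / 1.5]² = 19.8, so 20 control + 40 MSC = 60.

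The noncentral t version gives 21 + 42 = 63. The stated 74 is not reproduced by the method described. A three-group F test with means 0, 1.5 and 1.5 gives 74.5, but that is not the comparison described. The discrepancy is on the cautious side and does not decide this point. It shows that the pooled comparison has slack.

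**Step 2: effect of adjustment.** Residual SD = 1.68 × √(1 − R²). The standard error falls by 1 − √(1 − R²):

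- R² 0.05: 1 − 0.975 = 2.5%
- R² 0.10: 1 − 0.949 = 5.1%
- R² 0.20: 1 − 0.894 = 10.6%

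Power is from the noncentral t, two-sided 0.05, difference 1.5. The split of 74 is taken as 49 v 25 for the pooled comparison and 25 v 25 for one dose:

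| Assumed R² | Residual SD | Pooled, 60 v 30 | Pooled, 49 v 25 | One dose, 30 v 30 | One dose, 25 v 25 |
|---|---|---|---|---|---|
| 0 (t test) | 1.680 | 97.7% | 94.8% | 92.5% | 87.1% |
| 0.05 | 1.637 | 98.2% | 95.7% | 93.7% | 88.8% |
| 0.10 | 1.594 | 98.6% | 96.5% | 94.8% | 90.3% |
| 0.20 | 1.503 | 99.3% | 98.0% | 96.7% | 93.3% |

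**Step 3: price if the covariates explain nothing.** Spending 3 degrees of freedom at 25 v 25 takes them from 48 to 45. With the SD still 1.68, power goes from 87.1% to just under that (0.8714 to 0.8705).

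**Step 4: chance imbalance.** The SD of the difference in prevalence of a binary factor between two arms of 30 is √[p(1 − p) × 2/30]. The prevalence p is assumed, since the documents give none. For p = 0.2, 0.3 and 0.5 this is 0.103, 0.118 and 0.129. The probability that two given arms differ by 15 percentage points or more is then about 14%, 20% and 25%. For any one factor such an imbalance is possible but is not the expected outcome.

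**Step 5: are the covariates safe to use?** Under Study design, randomization takes place about a day before delivery. The first gel application follows suturing, and the pumps are masked. BMI, incision and closure are therefore settled before treatment starts, and adjusting for them does not condition on anything the treatment could have changed.

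**The case against.** The case against is substantial, and most of it stands.

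- **The test is valid.** Under randomization the unadjusted t test is unbiased, and its type I error rate already allows for chance imbalance. This stands: the cost is precision, not bias.
- **The primary comparison is not short of power.** This stands on the stated inputs. The planning SD of 1.68 is also a total SD, so if its source population is comparable, this variation is already in the sample size.
- **The Background speaks of infection, not VSS.** This stands. A reader might infer that the protocol itself names known predictors of the primary outcome. It does not: the link to scarring runs through abnormal healing and is indirect. Wound infection is, however, a secondary outcome and part of the trial's hypothesis.
- **Closure may not vary.** A reader might take the phrase about suturing to mean that each operator closes differently. The text does not say so. This is one department, the number of operators is not given, and the phrase may describe a single routine. The absence of a named closure method is detail that an article may leave to the full protocol.
- **Heterogeneity is already limited.** Participants are primiparous, aged 21–35, at term, non-smoking and without keloid history. BMI remains open.

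What survives is that the article does not leave the test open: it states t tests for the pooled and the single-dose comparisons. A better use of data that should already be in the records is available at almost no cost.

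**Conclusion.** This is a cheap improvement, not an error in the plan. The stated t tests are valid, and the pooled primary comparison has about 95–98% power without adjustment. At the assumed R² of 0.05 to 0.20, adjustment adds 0.5 to 1.6 points to the pooled comparison at 60 v 30. For one dose against placebo at 25 v 25 it adds 1.7 to 6.2 points (87.1% to 88.8–93.3%).

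The size rests wholly on the assumed R². If the covariates explain almost none of the VSS variance there is no gain, and the loss is negligible. The documents do not support calling imbalance likely, or claiming that closure differs between operators.

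**What to change.** 1. Copy BMI from existing records into the case report form. Do the same for incision type and closure type if they vary in the department; a factor that is constant needs no field and no model term.
2. Before unblinding, prespecify a linear model of 6-month VSS on treatment plus these pre-treatment covariates. Use it for both doses against placebo and for each dose against placebo.
3. Keep the unadjusted t tests as supportive analyses.

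The cost is a few data fields, a short addition to the analysis text, and 2–3 degrees of freedom. Recruitment, treatment and surgical practice do not change.

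### Withdrawing women from the study for cosmetic use in follow-up creates avoidable missing month-6 scar scores and undermines the intention-to-treat analysis

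*Protocol article*

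**What the plan says.** Interventions gives the rule and its reason: "Cosmetic use may affect wound function", and then "If participants use cosmetics in the follow-up period, they will be withdrawn from the study". The rule names no body site and does not say whether a withdrawn woman still attends the month-6 visit. The same section places the first application on the operating table and the other five on the following days in the ward.

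Statistical analysis states: "All analyses will be conducted on the intention-to-treat and per-protocol principles", and explains that "Regardless of whether participants received the randomized treatment, the intention-to-treat principle considers all of them as randomized". On missing data it says "A complete case analysis will be performed if missing data for the randomized participants accounts for less than 5% of total data", with multiple imputation above that limit, and separately "Dropouts will be included in the analysis by multiple imputations for missing data". It adds: "The effect that the per-protocol participants and missing data might have on results will be assessed via sensitivity analysis".

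The primary outcome is VSS at month 6. Table 2 schedules VSS at weeks 4, 12 and 24; the week-2 visit has only the REEDA scale and adverse events. Under Randomization, concealment, and blinding, the investigators undertake to make a reasonable effort to avoid missing data once women are randomised.

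**The concern.** A rule that takes a woman out of the study after treatment is complete protects nothing in her treatment. It only stops her outcome from being seen. The trial then has to model a score that it could have measured at a visit already scheduled, and the reason for the gap is a behaviour that arose after randomisation.

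If that behaviour is related to how the scar looks, the women whose scores are missing differ from those who remain, and the month-6 comparison can be biased. The link is plausible: the protocol itself ties cosmetic use to the wound, and its Discussion expects losses especially among nonresponders. But the documents do not state that cosmetic use follows scar appearance, and a rule covering cosmetics in general could be triggered by use that has nothing to do with the scar.

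**Working it through.** **Inputs.** From Sample size: mean VSS 4.50, SD 1.68, difference 1.5, 30 women per group, so 60 MSC against 30 placebo for the pooled primary comparison. Assumed, because the documents give no figure: the number and pattern of withdrawals, and a correlation of 0.6 between an earlier VSS and month-6 VSS.

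**Plan's own figure.** The stated total of 74 is not reproduced. For 2:1 allocation, placebo n = 1.5 × 1.68² × (1.960 + 1.282)² / 1.5² = 19.8, so 20 + 40 = 60 (63 with the t distribution). The figure errs on the large side, and this point does not depend on it.

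**Step 1: completers only, one-arm bound.** Remove the 6 highest month-6 scores of 30 placebo women and none from the MSC arms.
- Large-sample check: cutting the top 20% of a normal distribution lowers its mean by SD × φ(0.842)/0.80 = 1.68 × 0.280/0.80 = 0.59, leaving 1.50 − 0.59 = 0.91.
- Simulation with samples of 30 and 60 (40,000 trials, Welch t test): difference 0.93, power about 73%. With nobody removed: 1.50 and about 97.5%.

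**Step 2: the same loss, with imputation.** Six of 90 is 6.7%. Counted per woman, this is above the 5% limit, so imputation applies. Within each arm, regress month-6 VSS on one earlier VSS among the women kept, and predict the rest.
- Withdrawal driven by the month-6 score itself: about 1.1 (about 1.2 if the correlation is 0.8).
- Withdrawal driven by the earlier recorded VSS: about 1.5, so the bias is removed.

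**Step 3: graded withdrawal.** Here the probability of withdrawal rises smoothly with VSS by the same rule in every arm (true difference 1.50, correlation 0.6).

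| Driver of withdrawal | Withdrawn, placebo / MSC | Completers | Imputed |
|---|---|---|---|
| Unrelated to VSS | 10% / 10% | 1.50 | 1.50 |
| Month-6 VSS | 12.5% / 6.5% | 1.43 | 1.45 |
| Month-6 VSS | 23% / 13% | 1.38 | 1.42 |
| Month-6 VSS | 28% / 12% | 1.21 | 1.29 |
| Earlier VSS, same three settings | similar | 1.45, 1.43, 1.32 | 1.50 |

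**Step 4: balanced withdrawal.** Remove the worst 10% of each arm (3 of 30 and 6 of 60). With a true difference of 1.5, the estimate is about 1.51 and power about 98%. With no true difference, the estimate is about 0.01 and the rejection rate about 8% instead of 5%, because cutting off high scores narrows the observed spread.

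**Step 5: where imputation has little to use or is not applied.**
- A woman withdrawn before week 4 has no VSS at all (Table 2).
- 5% of 90 is 4.5. Read per woman, up to 4 losses fall under complete-case analysis. If all 4 were the worst placebo scars, the difference would be about 1.10 and power about 85%. The separate sentence that dropouts are imputed points the other way for the same women.

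**The case against.** The strongest reply is that the plan does not drop these women from the analysis. Statistical analysis keeps dropouts in by multiple imputation and adds sensitivity analyses, and Table 2 records VSS, erythema, pigmentation and thickness at weeks 4 and 12, which may predict month 6 well. Interventions also says that all participants are assessed through 6 months. Much of this stands:
- A reader might infer that the rule defeats the intention-to-treat analysis. The documents do not support that. It makes the analysis depend on an imputation assumption that observation would have made unnecessary.
- A reader might infer that imputation cannot repair the bias. Step 2 shows that it can, when recorded data explain the withdrawal.
- A reader might fear a false-positive result. With no true effect, removing the 9 worst of 60 MSC women and no placebo women gives a spurious benefit of about 0.45 and a rejection rate of about 24% among completers. But participants and assessors are blinded, so scar-driven withdrawal should be equal in expectation across arms under no effect. If 9 of 90 women leave regardless of arm, the chance that all 9 are MSC women is (60/90) × (59/89) × … × (52/82), about 2%. The scenario also ignores the planned imputation.
- Loss of power is not the main harm. The stated inputs need 60 to 63 women, so 90 leaves a margin of 27 to 30. Where the worst placebo scars leave, the bias is towards no effect.

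What does not stand is that imputation justifies the rule. A modelled score is a poorer substitute for one that could be measured. The statement that all participants are assessed does not say that it covers withdrawn women, and the ordinary meaning of withdrawal from the study is that it does not.

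**Conclusion.** The concern holds in a limited form. The cosmetics rule converts an observable primary outcome into missing data because of a post-randomisation behaviour, after all study applications have ended. It thereby undermines the as-randomised analysis and runs against the stated effort to avoid missing data.

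The size is not known. The fall from 1.50 to about 0.93 is a one-arm, complete-case bound. With imputation it lies between about 1.1 and no bias, depending on what drives withdrawal, and the graded scenarios give imputed differences of 1.29 to 1.50. These figures rest on normal scores, the protocol's mean, SD and difference, and the assumed correlation and withdrawal patterns. That withdrawal depends on the scar is a reasonable inference, not something the protocol says. The severity is below must-fix, but the correction is cheap and a missed month-6 score cannot be recovered later.

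**What to change.** Reconcile Interventions with Statistical analysis:
- Replace withdrawal by recording cosmetic use (product, site, dates) as a protocol deviation.
- Keep the woman in follow-up with all remaining assessments, unless she herself chooses to leave.
- Use her observed VSS in the intention-to-treat analysis and exclude her only from the per-protocol analysis.
- State which rule governs dropouts when less than 5% of data are missing: complete cases or imputation.

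The cost is a short amendment and one case report form field, with no extra women or visits. The small downside is that the intention-to-treat effect will include any effect of cosmetic use. The per-protocol analysis already planned addresses that question.
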